## Abstract

**Background:**

The number of incident cases and deaths from primary liver cancer, predominantly hepatocellular carcinoma (HCC), has increased markedly in the last two decades. HCC is generally diagnosed at an advanced stage, and most new cases are in people aged over 70 years with age-related comorbidities. Treatment options are often limited, with most patients receiving palliative treatment or supportive care only. As a consequence, maintaining quality of life (QoL) through symptom management is critically important and is a core objective of clinical care. Strong evidence supports the efficacy of supervised exercise training for addressing certain cancer-related symptoms, including QoL, physical function, and fatigue. However, there are many barriers to implementing supervised exercise programmes within cancer care pathways, including economic pressures on healthcare systems and personal barriers for patients. Recent advances in technology allow patients to exercise at home under the ‘virtual’ supervision of an exercise professional through videoconferencing software (termed ‘telehealth exercise’). Despite its potential, there are uncertainties relating to the feasibility, acceptability, and safety of telehealth exercise in people living with HCC.

**Methods:**

This is a protocol for a prospective, single-centre, single-arm, pretest-posttest feasibility trial. We aim to recruit 20 patients aged 60 years or older who have received treatment for HCC and are undergoing routine clinical monitoring. Patients will be invited to take part in two online, home-based, group exercise sessions per week for 10 consecutive weeks. The ‘virtual’ exercise sessions will be delivered in real time by an exercise professional through videoconferencing software. Each session will comprise 30 min of aerobic and resistance exercise performed at a moderate intensity, as guided by the 10-point Borg rating of perceived exertion scale. Feasibility outcomes include recruitment, retention, adherence, intervention fidelity, and safety. Acceptability of the intervention will be assessed using a mixed-methods approach via monthly online surveys and an exit telephone interview. Physical function, accelerometry-measured physical activity, mid-upper arm circumference, and patient-reported outcome measures (PROMS) will be assessed before and after the intervention to determine the feasibility of assessing outcome measures. Physical function outcomes include the short physical performance battery and Liver Frailty Index. PROMS include the Functional Assessment of Cancer Therapy-Hepatobiliary questionnaire, Functional Assessment of Chronic Illness Therapy-Fatigue questionnaire, Activities-specific Balance Confidence scale, Hospital Anxiety and Depression Scale, and the Godin Leisure-Time Exercise Questionnaire.

**Discussion:**

This mixed-methods study will address uncertainties relating to the feasibility and acceptability of delivering live, online, home-based, group exercise sessions to patients with HCC. The findings will inform whether any modifications are required to refine and optimise the intervention, and the assessment of outcome measures will provide information on the likely size and variability of intervention effects. Collectively, the data generated will inform the design of a subsequent, adequately powered, randomised controlled trial to evaluate the efficacy of the telehealth exercise intervention.

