## Methods

### Study design

TELEX-Liver Cancer is a prospective, single-site, single-arm, pretest-posttest feasibility trial. In addition to receiving standard care, patients will receive a 10 week, home-based, virtual, group exercise intervention delivered in real time by an experienced physiotherapist. Feasibility and acceptability of the intervention and outcome measures will be assessed using a mixed-methods approach. A schematic diagram of the study schedule is presented in Fig. 1. The study is prospectively registered on the International Standard Randomised Controlled Trial Number (ISRCTN) registry (ISRCTN14411809). A Standard Protocol Items: Recommendations for Interventional Trials (SPIRIT) checklist [24] is in the supplementary files.

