### Other intervention components

Patients will have the option of contacting a research team member via telephone or email for assistance if they have any questions or experience any issues, such as technical difficulties using the videoconferencing software. No concomitant care or interventions will be prohibited during the trial [24].

Patients will be able to retain their resistance bands and pedal exerciser at the end of the study to allow them to continue exercising at home after the study has finished. Tablets and accelerometers will be returned to the research team at the follow-up visit to the hospital.

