### Data and statistical analysis

#### Quantitative analysis

The flow of patients throughout the trial will be reported in a CONSORT flowchart. Descriptive statistics will be used to present baseline characteristics, feasibility outcomes, and acceptability survey responses. Continuous variables will be described with the mean and standard deviation (SD), and categorical variables will be reported as frequency and proportion. Continuous data with an asymmetrical distribution will be summarised with the median and interquartile range. A paired *t*-test or Wilcoxon signed-rank test (depending on data distribution) will be used to evaluate changes in outcomes from baseline to post-intervention, with the mean difference and 95% confidence interval from the model presented. Data will be analysed per protocol (i.e. missing data at follow-up will not be imputed).

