## Discussion

Patients with HCC typically face limited treatment options due to age-related morbidities and the advanced stage at which the disease is diagnosed. Most patients are not eligible for curative treatment and are offered palliative treatment or supportive care only [7]. As a consequence, maintaining QoL and day-to-day function through symptom management is critically important [10]. Strong evidence supports the efficacy of specific doses of supervised exercise training for addressing certain cancer-related symptoms, such as QoL, physical function, fatigue, and symptoms of anxiety and depression [11]. However, there are many barriers to implementing supervised exercise programmes within cancer care pathways, including economic pressures on healthcare systems and personal barriers for patients.

Telehealth exercise offers patients the opportunity to take part in virtually supervised group exercise in their own home [19]. This may remove some of the barriers for exercise participation and offers a relatively low-cost means of delivering exercise at scale for a patient population that covers a wide geographical location. Despite its potential, there are uncertainties relating to the feasibility, acceptability, and safety of telehealth exercise in people living with HCC.

This mixed-methods study will address uncertainties relating to the feasibility and acceptability of delivering live, online, home-based exercise to patients with HCC. The findings will inform whether any modifications are required to refine and optimise the intervention, and the assessment of outcomes will provide information on the likely size and variability of intervention effects. Collectively, the data generated will inform the design of a subsequent, adequately powered, randomised controlled trial to evaluate the efficacy of the telehealth exercise intervention.

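### A single-arm before-after change cannot give the likely size of an intervention effect, although the article says it will

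*Protocol article*

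**What the plan says.** The Study design section is explicit: "TELEX-Liver Cancer is a prospective, single-site, single-arm, pretest-posttest feasibility trial". Under Quantitative analysis, a paired t-test or Wilcoxon signed-rank test "will be used to evaluate changes in outcomes from baseline to post-intervention, with the mean difference and 95% confidence interval from the model presented". The same section adds: "Data will be analysed per protocol (i.e. missing data at follow-up will not be imputed".

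Three places attach a stronger meaning to these results:

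- The Abstract says that "the assessment of outcome measures will provide information on the likely size and variability of intervention effects".
- The main Discussion repeats it: "the assessment of outcomes will provide information on the likely size and variability of intervention effects".
- The second item under Aims and objectives joins the feasibility of measuring outcomes to a search for preliminary evidence that the intervention works.

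On the use of the results, the Abstract says that "the data generated will inform the design of a subsequent, adequately powered, randomised controlled trial to evaluate the efficacy of the telehealth exercise intervention". Table 1 (footnote) names FACT-Hep as the likely primary outcome of that trial. On background care, Other intervention components says: "No concomitant care or interventions will be prohibited during the trial".

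The article mentions no comparison group or external reference, and gives no caveat about attributing change to the exercise.

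**The concern.** An intervention effect is a contrast with what would have happened without the intervention. This trial observes only patients who receive it. The within-patient change therefore mixes any effect of the exercise with background change over the same ten weeks, and the direction of that background change is unknown. The article nevertheless presents the result as information on the size of the effect, placed directly before the sentence about an adequately powered randomised trial.

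Two things are at stake. One is what this trial may conclude: an improvement could be read as benefit, or a flat result as no benefit, when the design supports neither reading. The other is what is passed on. Effect size and variability are the two main inputs to a two-arm sample-size calculation, and only the second can be learned here.

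**Working it through.** **1. The plan's own figure.** Sample size gives at least 3 eligible patients per week, 30% consent and 6 months.

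- 26 weeks: 3 × 26 × 0.30 = 23.4
- 24 weeks: 3 × 24 × 0.30 = 21.6

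Both meet the stated minimum of 20. This is a recruitment projection; no outcome has a power calculation. The retention criterion of 75% corresponds to 0.75 × 20 = 15 completers, so 15 and 20 are used below.

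**2. What the paired change estimates.** Let τ be the mean intervention effect and β the mean change that completers would have shown anyway. Then

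E(follow-up − baseline) = τ + β.

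There is one observable quantity and two unknowns. A larger n narrows the interval around τ + β but never separates the terms. The article gives no ground for setting β to zero:

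- The Introduction describes symptoms of chronic liver disease as fluctuating.
- Patient identification and consent process describes entry as typically at a follow-up appointment after HCC treatment.
- Concomitant care is unrestricted.
- Only patients with follow-up data contribute, so the change is seen in a selected group.

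Recovery after treatment would push scores one way and disease progression the other, so the sign of β is unknown.

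**3. Precision, leaving bias aside.** The 95% half-width for mean change, in units of the SD of change, is t(0.975, n−1)/√n.

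- n = 20: 2.093/4.472 = 0.47
- n = 15: 2.145/3.873 = 0.55

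The 95% interval for an SD, as a multiple of its estimate, is √((n−1)/χ²) at the 97.5% and 2.5% quantiles.

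- n = 20: 0.76 to 1.46
- n = 15: 0.73 to 1.58

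A trial's sample size goes with the square of the SD. At n = 15 that is 0.732² = 0.54 to 1.577² = 2.49 times the planned size.

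**4. Consequence if the change were used as a target difference.** The values here are assumptions, not figures from the article: an observed change of 0.5 SD of the outcome, 90% power and a two-sided 5% test. With n per arm = 2(1.960 + 1.282)²/d² and power at 85 per arm = Φ(d√(85/2) − 1.960):

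| Background change | Effect left (d) | Needed per arm | Power with 85 per arm |
|---|---|---|---|
| 0 | 0.5 | 85 | 90% |
| +0.2 | 0.3 | 234 | 50% |
| +0.3 | 0.2 | 526 | 26% |
| −0.2 | 0.7 | 43 | over 99% |

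Step 3 uses the SD of change and step 4 the SD of the outcome. With equal SDs at both visits they are linked by √(2(1−r)), and they coincide when the baseline-to-follow-up correlation r is 0.5.

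**The case against.** The strongest reply is that nothing in this trial turns on these tests. The primary outcome is feasibility. The Outcomes section says the before-after measures are there to see whether they can be collected. The four criteria for success concern consent, attendance, questionnaire completion and serious adverse events. All of that is correct, and the feasibility verdict is unaffected.

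Several stronger readings are tempting, and the article does not support them:

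- **That the trial claims it will demonstrate efficacy.** The objective speaks only of preliminary evidence, and evaluation of efficacy is left to the randomised trial.
- **That the randomised trial will be sized on this change.** The text says only that the data, taken together, will inform its design. The table above shows a risk, not a stated plan.
- **That there is a multiplicity error.** Many outcomes will be compared, but Quantitative analysis states no significance level and no rule for declaring an effect. A family-wise error rate would rest on a threshold the article does not set, and on independence between outcomes that overlap (SPPB and LFI share chair stands and balance).
- **That recovery after treatment or regression to the mean will occur.** Both are possible, neither is established. The eligibility criteria set no time since treatment and do not select patients for poor scores on the outcomes tested.
- **That the whole sentence is wrong.** Estimating variability is a proper use of a feasibility study.

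What remains is the claim about size, made twice, and the efficacy objective. A fuller analysis plan could not rescue them, because the missing element is a comparator.

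**Conclusion.** The concern holds in a limited form. The article attributes to its outcome data a property that a single-arm within-patient analysis lacks at any sample size: information on the size of an intervention effect. This follows from the design and needs no numerical assumption beyond the absence of grounds for taking background change as zero.

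The size of the resulting error cannot be calculated from the documents. Under the assumed values, a background change of 0.2 SD in either direction moves the required size from 85 per arm to 234 or to 43. Separately from bias, 15 to 20 completers leave the mean change uncertain by about half an SD of the change either way. The variability aim stands, provided its imprecision is reported.

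**What to change.** - **Aims and objectives:** remove the efficacy part of the second objective and keep the feasibility of outcome assessment.
- **Abstract and Discussion:** remove the claim about the likely size of intervention effects. Keep variability.
- **Quantitative analysis:** report mean within-patient change with its 95% confidence interval descriptively, labelled as not attributable to the intervention. Do not use p-values as evidence of efficacy.
- **For planning the later trial:** report completeness, the SD and the baseline-to-follow-up correlation, the last two with 95% confidence intervals. State that the before-after change will not be used as that trial's target difference.

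The cost is a few sentences, the p-values and the efficacy wording. No data collection, patient burden or feasibility criterion changes.

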**Trial registration:**

ISRCTN14411809

**Supplementary Information:**

The online version contains supplementary material available at 10.1186/s40814-022-01069-1.

## Introduction

Primary liver cancer is the seventh most common cancer and third leading cause of cancer death worldwide, accounting for more than 8% of all cancer deaths [1]. Global cases of incident liver cancer and mortality are increasing. The Global Burden of Disease Study reported that from 1990 to 2017, the number of new liver cancer cases and liver cancer-related deaths has doubled [2]. In the United Kingdom (UK), liver cancer has shown the fastest rise in mortality rates for both males and females in the last decade [2]. There is also a strong relationship between liver cancer mortality and deprivation in England, as evidenced by the twofold higher mortality rates in the most deprived areas compared with the least deprived [3].

The most common type of primary liver cancer is hepatocellular carcinoma (HCC). HCC is generally diagnosed at an advanced stage, and most new cases are in people aged over 70 years with age-related comorbidities, such as frailty syndrome and sarcopenia [4, 5]. The majority of HCC patients in the UK are not eligible for curative treatment, and the prognosis of HCC is typically poor, with a median survival of approximately 6 months and 5-year survival rate of less than 15% [6, 7]. HCC is commonly accompanied by undesirable symptoms, including pain and fatigue [8], which have a negative impact on functional status and quality of life (QoL) [9]. As a consequence, maintaining QoL through symptom management is critically important and often a core objective of clinical care for patients with HCC [10].

A growing body of evidence supports structured exercise as an adjunct therapy in cancer care. The American College of Sports Medicine (ACSM) roundtable in 2018 reported that specific doses of exercise training can improve QoL, fatigue, physical function, anxiety, and depressive symptoms in people living with and beyond cancer [11]. The review also concluded that supervised exercise is more effective than strictly unsupervised programmes [11]. However, there are many barriers to successfully implementing supervised exercise programmes within cancer care pathways, including economic pressures on healthcare systems and personal barriers for patients. Inconvenient travel distances and a lack of access to appropriate facilities are key barriers to regular exercise for cancer survivors [12, 13], and most patients prefer home-based exercise [14–17]. Cancer survivors also report wanting more guidance on the type and specific characteristics of exercise (i.e. frequency, intensity, and duration) they can safely undertake [18]. The challenge is to develop effective exercise interventions that are accessible and sustainable and can be delivered across local healthcare providers [16].

Recent advancements in videoconferencing technology allow patients to exercise at home under the ‘virtual’ supervision of an exercise professional, termed ‘telehealth exercise’ [19]. The exercise instructor can guide patients through the exercise in real time, mimicking the delivery of traditional facility-based exercise training without the need for travel or access to facilities. Moreover, virtual exercise sessions can be delivered in a group-based format, which may provide a peer-supportive environment. Thus, there is potential for telehealth exercise to optimise the health-related benefits of exercise through expert supervision whilst also circumventing common barriers to exercise and meeting the preferences of cancer survivors.

Despite the potential of telehealth exercise, there are uncertainties regarding its feasibility and acceptability in people living with and beyond cancer. One recent study reported that delivering live, online, group-based exercise to highly functioning older adults via a videoconferencing platform is safe and feasible, as evidenced by no adverse events and high adherence (90%) and satisfaction rates [20]. Another recent study reported no intervention-related adverse events and reasonable adherence (79%) to an online falls prevention programme delivered via videoconference in older adults with mild cognitive impairment [21]. However, a 2020 rapid review of telehealth exercise interventions for cancer survivors found that no studies have used real-time videoconferencing to support the delivery of home-based exercise [22]. There are several considerations that may limit the uptake of telehealth exercise in patients living with HCC, including the need to consistently adhere to online exercise whilst managing the fluctuating symptoms associated with chronic liver disease. Unaddressed issues relating to acceptability and feasibility of telehealth exercise could undermine an evaluation of intervention efficacy [23]. Therefore, in line with Medical Research Council guidance on developing and evaluating complex interventions [23], this study will assess the feasibility, acceptability, and safety of delivering a 10-week telehealth exercise intervention to older patients with HCC. The findings will inform the design of a subsequent, adequately powered, evaluative randomised controlled trial (RCT).

### Aims and objectives

To examine the feasibility, acceptability, and safety of the telehealth exercise intervention in older patients with HCCTo assess the feasibility of assessing physical function and patient-reported outcome measures (PROMS) and glean preliminary evidence for the efficacy of telehealth exercise in older patients with HCCTo address the key uncertainties relating to intervention feasibility and acceptability to inform the design of a subsequent randomised controlled trial

## Methods

### Study design

TELEX-Liver Cancer is a prospective, single-site, single-arm, pretest-posttest feasibility trial. In addition to receiving standard care, patients will receive a 10 week, home-based, virtual, group exercise intervention delivered in real time by an experienced physiotherapist. Feasibility and acceptability of the intervention and outcome measures will be assessed using a mixed-methods approach. A schematic diagram of the study schedule is presented in Fig. 1. The study is prospectively registered on the International Standard Randomised Controlled Trial Number (ISRCTN) registry (ISRCTN14411809). A Standard Protocol Items: Recommendations for Interventional Trials (SPIRIT) checklist [24] is in the supplementary files.

**Fig. 1 Fig1:**
[figure not shown]
Schematic diagram of the study schedule. FACIT-F, Functional Assessment of Chronic Illness Therapy-Fatigue; FACT-Hep, Functional Assessment of Cancer Therapy-Hepatobiliary; ABC scale, Activities-specific Balance Confidence scale; HADS, Hospital Anxiety and Depression Scale

### Study setting

Participants will be recruited from outpatient liver cancer clinics at the Liver Unit at Newcastle upon Tyne Hospitals NHS Foundation Trust (NuTH), UK. It is anticipated that patients will be recruited over a 6-month period. NuTH is the study sponsor. The virtual supervised sessions will be delivered by an NHS-employed physiotherapist, and patients will complete the exercise sessions at home.

### Participant eligibility

#### Inclusion criteria

Clinical diagnosis of HCCAged 60 years or olderHave received NHS standard treatment for HCC (determined by stage of disease), with post-treatment imaging reporting a complete response, partial response, or stable diseaseCurrently undergoing ‘active monitoring’ at NuTH, involving routine imaging scans and outpatient visits every 3–6 monthsChilds-Pugh of B7 or lower (i.e. preserved liver function)World Health Organization performance status of 0 or 1Minimum life expectancy of 6 monthsWilling and able to give written informed consent

#### Exclusion criteria

Aged less than 60 yearsUncontrolled cardiovascular or metabolic diseaseBreathlessness at rest or with mild exertionSevere resting hypertension or (≥ 180/100 mmHg) or tachycardia (≥ 100 bpm)Inability to understand written and verbal instructions in EnglishPhysical disability or mental impairment that precludes safe and adequate participation in the study

